#### Interim analyses

We plan to analyze descriptively the data collected at baseline to check for balances in baseline characteristics of samples from all treatment arms. This will be done in December 2025. We will also provide descriptive analysis on the pre-existing quality of care received by mothers in maternity departments of our study hospitals, as well as characteristics of midwife champions selected. These descriptive analyses will feature in a baseline report that will be made publicly available.

#### Methods for additional analyses

We will also leverage the fact that the OTIP Champions Program was implemented at scale in Ghana to complement our cRCT with an approach that allows us to look at mortality impacts. We will compare outcomes for hospitals that received OTIP with those that were not part of the program. Because the former set of hospitals might differ from the latter set in unobservable ways, we will use a regression discontinuity design (RDD). The intuition of RDD is that if OTIP affects outcomes, we would observe abrupt jumps in outcomes at a pre-determined eligibility threshold. Leveraging the arbitrary cutoff of 1,200 deliveries in 2022 for eligibility into the OTIP program, which can be deemed as good as random, we can robustly estimate impacts for all hospitals around the threshold.

The key assumption of the RDD strategy is that subject to no jumps in other unrelated characteristics, the jump in eligibility makes hospitals just above and just below the threshold comparable, in all characteristics, except in outcomes affected by OTIP. This key assumption can be tested by examining how variables unrelated to OTIP (such as A&E admissions) behave around the threshold.

To estimate the impacts of OTIP using RDD, we use the following specification for hospital$$\:\:i$$:$$Y_i=\alpha+\beta\;del_i+\gamma\;Above_i+\epsilon_i$$

Where $$\:del$$ is the number of annual deliveries (the running variable) in hospital$$\:\:i$$ in 2022 and $$\:Above$$ is an indicator for whether hospital$$\:\:i$$ had more than 1,200 deliveries in 2022.

Our estimate of interest will be $$\:\gamma\:$$, which is the estimate for the difference in the outcome of interest attributed to OTIP. $$\:{Y}_{i}$$ represents the mortality rate during a period (monthly or annual). As a placebo test, we will present effects in mortality for the outcomes measured before the nationwide roll-out of OTIP in Ghana.

As the estimate of $$\:\gamma\:$$ is dependent on the functional form of the data, that is, how $$\:Y$$ changes with $$\:{del}_{i}$$, we will explore second order polynomials, if necessary, to get a better estimate of $$\:\gamma\:$$.

A key aspect of the RDD is defining a window of analysis around the OTIP eligibility threshold in the running variable (2022 deliveries). We will explore optimal bandwidths for this analysis.

Furthermore, the data gathered will be able to answer more scientific questions than outlined in this protocol. The study team expects to conduct and publish additional analyses.

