#### Data collection and management

We will rely on two main sources of data. For the cRCT, we will mainly rely on primary collected data from patients (mothers), and from midwives through in-person interviews. To promote data quality, all enumerators attend a week-long training session before data collection. This includes classroom-based training as well as training in hospital settings. It also covers how informed consent should be obtained, implying that informed consent will be acquired by well-trained and vetted data collection staff before the commencement of any data collection. Lead enumerators were also involved in two weeks of extensive piloting of the survey instruments.

For the regression discontinuity design, we will utilize the District Health Information Management System II (DIMS II), an electronic platform managed by GHS to collect, record, and analyze health service data nationwide. We will use key indicators such as deliveries and mortality for mother and new-born pairs at the hospital and monthly level from before, during and after OTIP implementation.

Administrative records and collected data will be recorded electronically using password-protected laptops. Once data collection is completed, all data will be promptly uploaded to an encrypted folder and/or deleted from the laptops. Access to the encrypted folder will be restricted to the research team, with participants’ identities anonymized in any reports derived from the research.

Once results are published, an anonymized version of the dataset will be released publicly without any personally identifying information.

The project is compliant with the Ghana Data Protection Act 2012 Act 846, and the UK Data Protection Act 1998.

For further details on data management: please refer to the project’s management registration: https://ifs.org.uk/sites/default/files/2024-11/Data-protection-V2.pdf. Data availability is outlined in online supplemental material S2.

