#### Statistical methods

For our process variables, we will estimate the intent-to-treat effect of the program. Our design is a cluster randomized controlled trial stratified by region.

We estimate the impact of OTIP on process and maternal and neonatal outcomes by estimating the following specification for the outcome *Y* of mother or baby *i* in hospital *j* in region *r* at time *t*:2$$Y_{ij}=\beta\;OTIP_j+\delta\;X_{ij}+Y_r+\epsilon_{ij}$$.

Where $$\:OTI{P}_{j}$$ indicates if a hospital is allocated to receive OTIP early, $$\:{\varvec{X}}_{ij}$$ is a vector of controls for hospital characteristics selected by machine learning methods, and $$\:{\gamma\:}_{r}$$ are region fixed effects, as we stratified our randomisation by region to ensure balance in earlier and later treated hospitals in each region.

To increase statistical power, we will leverage the panel nature of our data and use baseline values of the outcomes in our analysis. For observations with values collected at baseline and follow-up, we can use an ANCOVA design. For observations without baseline values, we can use a difference-in-differences specification, exploiting variation across early- and later-treated hospitals, before and after the introduction of OTIP in early-treated.

To investigate mechanisms behind the observed impacts, we will use the same design with hospital staff outcomes to understand whether any impacts are driven by changes in staff outcomes due to OTIIP, such as midwives’ clinical knowledge and attitudes.

Moreover, for outcomes with low serial correlation, we will follow [15] and pool the multiple follow-up measurements to average out noise and increase power.

Due to the small number of clusters (25), we will present a wild-bootstrap p-value that is robust to small numbers of clusters [16]. We will additionally adjust for multiple hypothesis testing by family of outcome. Lastly, we will test for balance using baseline data for outcomes for hospital, midwives and patients’ characteristics. We will also test if attrition is uncorrelated to treatment allocation, and in case of non-random attrition on treatment status, we will estimate our main specification using inverse probability weighting.

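### The complementary regression discontinuity model for mortality omits the hospital's own pre-roll-out mortality, giving up precision that data already planned for extraction could supply

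*Protocol article*

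**What the plan says.** Under Methods for additional analyses, the Protocol article introduces the RDD to "complement our cRCT with an approach that allows us to look at mortality impacts". The equation is written out: hospital mortality (monthly or annual) on an intercept, 2022 deliveries and an indicator for being above the cutoff. The coefficient γ on that indicator is the estimate of interest. The refinements named are a second-order polynomial, if needed, and the choice of bandwidth. No covariate is named.

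Under Data collection and management, the RDD is to draw on national administrative indicators, namely "deliveries and mortality for mother and new-born pairs at the hospital and monthly level from before, during and after OTIP implementation". Mortality before the roll-out is then given one stated role: "As a placebo test, we will present effects in mortality for the outcomes measured before the nationwide roll-out of OTIP in Ghana".

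The Statistical methods section does use baseline outcomes: "To increase statistical power, we will leverage the panel nature of our data and use baseline values of the outcomes in our analysis". That paragraph is written for the cluster randomised trial, comparing early- with later-treated hospitals. The RDD compares hospitals on either side of the 1,200-delivery cutoff. It has its own equation, which does not carry the baseline term over.

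**The concern.** A hospital's mortality rate tends to persist, because case mix, referral role and staffing change slowly. Part of the residual variance in the later rate is then predictable from the earlier rate, and leaving it in the error term widens the interval for γ. The RDD can least afford this: it uses only hospitals near one cutoff, and its outcome is rare. The placebo test can show a chance gap at the cutoff before the roll-out, but it does nothing to γ. A covariate takes out the part of that gap that carries forward.

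**Working it through.** **Nothing to reproduce.** The article gives no sample size, standard error, power or detectable effect for the RDD. It also gives no correlation between earlier and later hospital mortality. The size of the gain is therefore conditional.

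**Step 1: general formula.** With the pre-roll-out rate added, SE(adjusted)/SE(stated) ≈ sqrt(1 − ρ²), where ρ is the pre/post correlation given deliveries and the indicator.

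| ρ | SE ratio | SE reduction | Equivalent number of hospitals, 1/(1 − ρ²) |
|---|---|---|---|
| 0.3 | sqrt(0.91) = 0.954 | about 5% | 1.10 times |
| 0.5 | sqrt(0.75) = 0.866 | about 13% | 1.33 times |
| 0.7 | sqrt(0.51) = 0.714 | about 29% | 1.96 times |

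The covariate costs one residual degree of freedom, a factor sqrt((n − 3)/(n − 4)). With an assumed n = 30 hospitals in the bandwidth this is sqrt(27/26) = 1.019. So at ρ = 0 the SE would rise by about 2%, and at ρ = 0.5 the ratio would be 0.866 × 1.019 = 0.883.

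**Step 2: which ρ is plausible.** Inputs from Study setting (high-volume hospitals, 2023): neonatal mortality 8.21 per 1,000 and maternal mortality 110 per 100,000. At 1,200 deliveries, taking deliveries as live births:
- neonatal: 1,200 × 0.00821 = 9.85 deaths a year
- maternal: 1,200 × 0.0011 = 1.32 deaths a year

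Assume Poisson counts, true rates stable over time, and a between-hospital coefficient of variation CV. With one post-year and k pre-years, and μ expected deaths a year:

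ρ = CV² / sqrt[(CV² + 1/μ)(CV² + 1/(kμ))]

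Example, neonatal, CV = 0.3, k = 1: 0.09/(0.09 + 0.1015) = 0.47. Maternal, same settings: 0.09/(0.09 + 0.7576) = 0.11.

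| Assumed CV | Neonatal ρ (k = 1; k = 2) | Maternal ρ (k = 1; k = 2) |
|---|---|---|
| 0.2 | 0.28; 0.35 | 0.05; 0.07 |
| 0.3 | 0.47; 0.55 | 0.11; 0.14 |
| 0.5 | 0.71; 0.77 | 0.25; 0.31 |
| 0.7 | 0.83; 0.87 | 0.39; 0.47 |

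The article gives no CV; the range is an assumption.

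**Step 3: single-month rates.** At an assumed 100 deliveries a month (0.82 neonatal and 0.11 maternal deaths expected) and 24 pre-months, CV 0.3, 0.5 and 0.7 give ρ of 0.21, 0.38 and 0.51 for neonatal mortality (SE ratio 0.98, 0.93, 0.86). For maternal mortality they give 0.04, 0.10 and 0.17 (SE ratio 0.985 or above).

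**Step 4: simulation of the stated RDD with and without the covariate.** Assumptions: 6,000 runs, hospitals within 400 deliveries of the cutoff, annual rates, two pre-years, no true effect. SE ratios:

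| Assumed CV | Neonatal, 30 / 60 hospitals | Maternal, 30 / 60 hospitals |
|---|---|---|
| 0.2 | 0.96 / 0.94 | 1.02 / 1.01 |
| 0.3 | 0.86 / 0.84 | 1.01 / 1.00 |
| 0.5 | 0.66 / 0.64 | 0.96 / 0.96 |
| 0.7 | 0.51 / 0.51 | 0.90 / 0.88 |

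The mean estimate stayed close to the true value of zero in both models, so the difference is one of precision only.

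**The case against.** A running variable and a threshold indicator without covariates is a standard RDD, and leaving out the earlier rate does not bias γ. The article is a condensed account, the RDD is an additional analysis, and its wording on polynomials and bandwidth is provisional. Precision covariates could be settled in a fuller document. The lack of bias stands. The rest weakens the point without removing it: the article commits to an explicit equation and names its refinements, and baseline adjustment is not among them, although the authors adopt it for the randomised comparison.

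The objection on size largely stands. The CVs are assumed, and drift in true rates would lower ρ. Maternal mortality and single-month rates offer little or no gain, and with 30 hospitals the maternal SE could be up to about 2% worse.

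A reader might also infer more than the article supports:
- *That the trial already holds these data.* The article says only that they will be used.
- *That the plan restricts them to the placebo test.* That is the only use it states; it does not exclude others.
- *That this is the trial's main mortality estimate.* The RDD is described as complementary, and Outcomes lists maternal and neonatal mortality among the trial's primary outcomes too.
- *That adjustment removes chance pre-period gaps.* It subtracts the fitted coefficient times the gap, and that coefficient is attenuated when the earlier rate is noisy, as it is with about 1.3 maternal deaths a year.

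**Conclusion.** The point holds as one of efficiency. The RDD equation omits a pre-treatment predictor that the plan already intends to extract, and the validity of γ is not in question. For ρ between 0.3 and 0.7 the SE would fall by about 5% to 29%, but the article does not give ρ and no single figure should be attached. Under Poisson counts, stable true rates and assumed CVs of 0.2 to 0.7, the gain is plausible for annual neonatal mortality, ranging from slight at the lowest CV to large at the highest. It is small or nil for maternal mortality unless hospitals differ widely, and generally small for single-month rates. The change is worth making because it is cheap. Naming the adjusted model in advance also avoids choosing between the two after the results are seen.

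**What to change.** Extend the RDD equation by one term: Y_i = α + β·del_i + γ·Above_i + θ·Ypre_i + ε_i. Here Ypre_i is the hospital's own rate of the same outcome, averaged over a fixed window that ends before the first roll-out phase. State the window's dates. Make this the pre-specified main RDD estimate, at least for neonatal mortality, report the unadjusted estimate as a sensitivity analysis, and keep the placebo test as planned.

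No new data source is needed. The costs are:
- one residual degree of freedom, and possibly a slightly larger SE for maternal mortality if few hospitals fall within the bandwidth;
- a rule for hospitals without pre-period records, such as a missing-data indicator or inclusion only in the unadjusted analysis;
- a rule for hospitals with earlier pilot exposure. Stopping rules says that OTIP has been piloted and implemented in Ghanaian hospitals since 2012, so the window may not be untreated everywhere. Eligibility criteria says when the first two phases were complete but not when the first began, so that date has to be fixed.

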#### Study setting

The Government of Ghana, through Ghana Health Services, is rolling out OTIP to all high-volume hospitals (defined as hospitals with more than 1,200 births in 2022) in different regions of the country. In 2023, the average total number of deliveries in these high-density hospitals was 2,146. The average maternal mortality rate was 110 per 100,000 live births, and the average neonatal mortality rate was 8.21 per 1,000 live births. In hospitals across Ghana, the average total number of deliveries in 2023 was lower, at 1,688. The average maternal mortality rate was slightly higher at 126 per 100,000 live births, while the average neonatal mortality rate was slightly lower at 7.7 per 1,000 live births.

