#### Participant timeline

Hospitals were randomized into early and late treated in July 2024. Pre-intervention implementation data was collected in September 2024. The first set of OTIP trainings took place in October 2024, the second will be conducted in February 2025. Data collection for primary outcome analysis will be conducted in January 2025. Mothers for the impact analysis will be recruited from early January 2025 and data collection is expected to take one month. The participant timeline is presented in Fig. 3.

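### The mortality regression discontinuity forces one volume slope on both sides of 1,200 deliveries and fixes no post-training outcome window, so the estimated jump can absorb a slope change or be diluted by roll-out months

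*Protocol article*

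**What the plan says.** Methods for additional analyses in the protocol article gives the model as Y = α + β·del + γ·Above + ε for each hospital. Here del is the number of deliveries in 2022, and Above is 1 if the hospital "had more than 1,200 deliveries in 2022". The coefficient γ is the estimand, "which is the estimate for the difference in the outcome of interest attributed to OTIP". Y is a mortality rate, monthly or annual, with no calendar period named.

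The section recognises that γ depends on functional form and answers that "we will explore second order polynomials, if necessary". It calls the choice of window important and leaves the bandwidth to be explored. It adds one falsification check: "As a placebo test, we will present effects in mortality for the outcomes measured before the nationwide roll-out of OTIP in Ghana".

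On timing, Eligibility criteria says that the first two roll-out phases were finished by April 2024. Methods and trial design assigns 12 of the last 25 hospitals to early training and 13 to training about four months later. Participant timeline places the first trainings in October 2024 (Methods and trial design says September) and says that "the second will be conducted in February 2025". Data collection and management says that the monthly hospital data for this analysis cover the time preceding, during and following implementation.

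**The concern.** The model has no Above × del term, so it fits parallel lines on the two sides of the cutoff. If the true volume–mortality relation bends near 1,200, parallel lines cannot follow it, and the misfit goes partly into γ. A quadratic common to both sides bends smoothly through the cutoff and still cannot reproduce a change of slope there.

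The second matter is timing. Above is fixed by 2022 volume and does not change when a hospital is trained. Until February 2025 some hospitals with Above = 1 have not had the programme. If their untrained months enter the main estimate, γ is a mixture of treated and untreated time, yet it would be reported as the effect of OTIP.

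Both matter because this analysis is introduced as the one that lets the study examine mortality. A few tenths of a death per 1,000, or an effect cut by a fifth or a half, could change how the result is read.

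**Working it through.** The protocol gives no power, detectable effect or bandwidth for this analysis, so there is no stated figure to reproduce. Two checks follow.

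**1. False jump from a slope change**

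Assumed: no true jump; neonatal mortality rises by 2 per 1,000 per 1,000 deliveries below 1,200 and is flat above. The kink and the hospital distributions are illustrations, not figures from the protocol. Let x = (del − 1,200)/1,000. Least squares on the protocol's model gives

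- common slope b = (pL·VL·βL + pR·VR·βR)/(pL·VL + pR·VR), where p is the share of hospitals on each side, V the variance of x on that side and β the true slope there;
- γ = (mean Y above − mean Y below) − b × (mean x above − mean x below).

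Worked case, hospitals evenly spread over 0–3,600 deliveries: pL = 1/3, VL = 1.2²/12 = 0.12, pR = 2/3, VR = 2.4²/12 = 0.48. So b = (1/3 × 0.12 × 2)/(1/3 × 0.12 + 2/3 × 0.48) = 0.08/0.36 = 0.222. Mean Y differs by 0 − (2 × −0.6) = 1.2, and mean x differs by 1.2 + 0.6 = 1.8. Hence γ = 1.2 − 0.222 × 1.8 = +0.80, when the truth is 0.

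The same projection in other windows (false jump per 1,000; falling density means proportional to exp(−del/900)):

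| Window (deliveries) | Density | Common slope | Common quadratic | Separate slopes |
|---|---|---|---|---|
| 0–3,600 | even | +0.80 | −0.14 | 0 |
| 0–3,600 | falling | +0.05 | −0.13 | 0 |
| 0–2,400 | falling | −0.44 | +0.06 | 0 |
| 700–1,700 (±500) | falling | −0.09 | +0.01 | 0 |
| 900–1,500 (±300) | falling | −0.03 | +0.004 | 0 |
| ±500 or ±300 | even | 0 | 0 | 0 |

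A cruder imbalance within ±500, with 30% of hospitals above the cutoff and an even spread on each side, gives b = 0.7 × 2 = 1.4 and γ = 0.5 − 1.4 × 0.5 = −0.20.

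For scale, Study setting gives a neonatal mortality of 8.21 per 1,000 in high-volume hospitals. So 0.80 is 9.7% of it, 0.44 is 5.4%, 0.20 is 2.4%, 0.09 is 1.1% and 0.03 is 0.4%.

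An uneven spread is plausible in a wide window. Study setting puts mean 2023 deliveries in the high-volume hospitals at 2,146, which is 2,146 − 1,200 = 946 above the cutoff, while the lower side can extend at most 1,200.

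**2. Dilution from roll-out months**

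With a constant effect and complete uptake, γ = (share of hospital-months with Above = 1 that follow training) × effect. The number of phase 1–2 hospitals is not given; 25 to 100 is assumed.

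- The 25 phase-3 hospitals in calendar 2024: 12 hospitals × 2 or 3 months after training, over 25 × 12 = 300 hospital-months, is 24/300 = 8% to 36/300 = 12%.
- All eligible hospitals in calendar 2024, 25 in phases 1–2: (25 × 8 + 24)/600 = 37% to (25 × 12 + 36)/600 = 56%.
- The same with 100 in phases 1–2: (100 × 8 + 24)/1,500 = 55% to (100 × 12 + 36)/1,500 = 82%.
- Single months, November 2024 to January 2025: 37/50 = 74% to 112/125 = 90%.

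The low ends count phases 1–2 as trained from May 2024 and the high ends as trained all year. In months after the last training the share is 100%.

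**The case against.** The plan does not intend to fit all hospitals. It speaks of estimating effects around the threshold and will look for an optimal bandwidth. In local windows with a falling density the false jump is about 1% of the mean neonatal rate or less, and a quadratic removes most of it. The pre-roll-out placebo could also expose a long-standing kink as a jump where none should exist. This stands, and it limits the size of the slope problem. It does not remove it: no bandwidth is fixed, the number of hospitals near 1,200 is unknown, and the quadratic is conditional on a need that is not defined.

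On timing, coding by eligibility is a legitimate intention-to-treat contrast. A reader might infer that the plan pools untrained months into its main estimate. The text does not say so: the list of data periods describes what is collected, and the early months serve the placebo. What stands is narrower: the outcome window is open while γ is attributed to OTIP, and a placebo confined to earlier months cannot detect dilution during roll-out.

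A reader might also take eligibility by births ("defined as hospitals with more than 1,200 births in 2022") against eligibility by deliveries ("Leveraging the arbitrary cutoff of 1,200 deliveries in 2022 for eligibility into the OTIP program") as evidence of misclassified hospitals. Study setting uses both words for the same hospitals in adjacent sentences. This is loose wording, and nothing shows that any hospital is on the wrong side.

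**Conclusion.** The point holds in limited form. As written, the model can turn a change in the volume–mortality slope into a jump. Under the assumed kink the error lies between −0.44 and +0.80 per 1,000 in wide windows. Within ±500 deliveries it is about 0.1 or less under the falling density, and 0.2 under a 30:70 split. Its sign depends on the window and the distribution of hospitals, so its direction cannot be assumed. Separate slopes remove it in every case tried.

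Two stronger readings are not supported. One is that the mortality estimate is off by a tenth: that figure needs the assumed kink and no bandwidth at all. The other is that the error disappears only when hospitals are spread symmetrically. The same falling density gives +0.05 over 0–3,600 and −0.44 over 0–2,400, so asymmetric cases can also cancel.

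Dilution is conditional on roll-out months entering the main estimate. If calendar 2024 were used, 37% to 82% of the effect would remain, given 25 to 100 hospitals in phases 1–2, a constant effect and complete uptake.

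**What to change.** Make the primary regression discontinuity a local linear model centred at 1,200 with separate slopes:

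Y = α + β·(del − 1,200) + γ·Above + δ·(del − 1,200)·Above + ε,

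fitted within the chosen bandwidth. Restrict the main estimate to months after the last eligible hospital is trained, which on the stated schedule means after February 2025. Keep the common-slope and quadratic fits as sensitivity analyses.

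Two refinements are optional and concern precision; their absence is not an error. One is each hospital's pre-roll-out mortality as a covariate. The other is deliveries as weight or exposure. At the 110 maternal deaths per 100,000 in Study setting, a hospital with 1,200 births expects 1,200 × 0.0011 = 1.32 maternal deaths a year, with a chance standard deviation of √(0.0011/1,200), about 96 per 100,000.

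The cost is a few lines of plan text and code, one more slope to estimate, and the loss of roll-out months from the main estimate. No new data are needed beyond enough follow-up after the last training.
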